#### Intervention group—continuous passive paracentesis

Ultrasound-guided (Ultrasound GE Vivid T8®) placement of an intra-abdominal double lumen catheter, Kit Certofix® Duo720, or similar, for paracentesis.Aseptic Seldinger technique, with an acute angle of percutaneous needle insertion.Adhesive, suture-free, abdominal wall catheter fixation.Continuous passive ascitic fluid drainage, preferentially through the proximal lumen (lateral opening) to minimize obstruction.Collection of ascitic fluid every 48 h for laboratorial and microbiological analyses.The trial intervention catheter will be in place for a maximum duration of 7 days.The catheter should be removed after 7 days of intervention or prior to ICU discharge, whatever occurs first.After the 7th day of intervention, paracentesis should be performed using the standard LVP approach as needed.

The 7-day duration of the intervention was determined based on previous studies revealing that the cumulative prevalence of IAH reaches a relative steady-state 5 days after ICU admission, with a median ICU stay of between 5 and 8 days in the studied populations [17, 18]. Furthermore, the impact of IAH on renal disfunction, assessed by the rise in serum creatinine, may lag up to approximately 3 days [19]. Therefore, we considered reasonable a period of 7 day for the trial intervention, while minimizing the risk of paracentesis catheter-associated infection, albeit considered safe [20–22].

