### Outcomes {12}

The primary outcome is serum creatinine concentration. The secondary outcomes are IAP, measured creatinine clearance, daily urine output, the multiorgan disfunction score Chronic Liver Failure Sequential Organ Failure Assessment (CLIF-SOFA) [13] and the incidence of stage 3 acute kidney injury (AKI) (defined by Kidney Disease: Improving Global Outcomes—KDIGO AKI [29] score), as well as 28-day renal replacement therapy (RRT)-free days, 28-day survival rate, and ICU LOS. The outcomes variables will be assessed at day seven (D7) after randomization (D0), unless otherwise stated. Additionally, IAP, serum creatinine concentration, measured creatinine clearance, daily urine output, and CLIF-SOFA will be analyzed using their maximum or minimum and daily mean values between D1 and D7.

Whenever ICU discharge or liver transplant occurs before D7, the last available data prior to these events will be used for outcome assessment. Additionally, stage 3 AKI will be considered when RRT or death occurs and, in these circumstances, a serum creatinine concentration value of 4 mg/dL and creatinine clearance value of 10 mL/min will be used for outcome assessment as mentioned in the literature [13, 29, 30].

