### Sample size {14}

The sample size was calculated using the statistical noncentral *t *function, with a one-sided alpha level of 0.05 [31]. The calculations were based on the expected renal function and IAP variation between groups, since we assume the former to be dependent of the latter.

To support the trial rationale of an expected clinically significant IAP decrease of 3 mmHg in the intervention group, a total of 44 patients are considered necessary to detect a statistically significant difference, with 1:1 allocation ratio, 80% statistical power, and 95% confidence level. This estimate is based in a post-hoc analysis of 61 patients with cirrhosis from a multicentric randomized controlled trial in shock patients where a mean difference in IAP of 3 mmHg was found between survivors and non-survivors (13.7 ± 3.9 and 16.7 ± 3.9 mmHg, respectively) [4].

Regarding the primary outcome, to detect a clinically and statistically significant decrease in serum creatinine of 0,4 mg/dL in the intervention group, a total of 60 patients is estimated, with a 1:1 allocation ratio, 95% statistical power, and 95% confidence. This estimate is based on a multicentric observational study of acutely decompensated patients with cirrhosis. In this study, cirrhotic acute-on-chronic liver failure patients with at least one organ failure had a mean creatinine difference of 0,4 mg/dL between survivors and non-survivor groups (0.9 ± 0.45 and 1.3 ± 0.48 mg/dL) [32].

We arbitrarily estimate that protocol non-adherence/attrition or violation after randomization may affect approximately 15% of cases and, therefore, to ensure that the number of patients that complete the protocol is reached for the primary outcome, the total sample size is set at 70 patients with a 1:1 group allocation ratio.

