## Data collection and management

### Plans for assessment and collection of outcomes {18a}

The assessment and collection of trial data will start at patient enrollment (D0) including vital signs, specific therapies (i.e., albumin, transfusions), vital organ support, blood, urine, and ascitic fluid tests, repeatedly up to D7.

The trial protocol includes the daily collection of an 8-h (480 min) urine volume, at blocked nocturnal interval from 23 to 07 h, for measurement of creatinine clearance, based on the following formula: creatinine clearance (mL/min) = (urinary creatinine [mg/mL] × urine volume [mL])/(serum creatinine [mg/mL] × urine collection time [480 min]) [34].

Daily blood analysis includes complete hemogram, coagulation, and biochemistry and arterial blood gas. Ascitic fluid will be collected with every new paracentesis and repeated every 48 h in the intervention group for screening of infectious complications.

Collected trial variables are mainly included in clinical severity scores APACHE II [35], SAPS II [36], CLIF-C ACLF [37], CLIF-SOFA, SOFA [38], RIFLE [30], KDIGO [29], ICA-AKI [13], MELD [39], and MELD-Na [40] and incorporate liver disease etiology, precipitant event for critical illness, urine output, serum creatinine, estimated and measured creatinine clearance, and number of days on RRT, Glasgow coma score and West-Haven scale, number of days under vasopressor support and dosage, PaO_2_/FiO_2_ ratio, positive end-expiratory pressure and number of days under mechanical ventilation, total bilirubin, coagulation international normalized ratio, platelet count, arterial blood lactate and prescribed albumin dosage. Intermediate effect variables IAP and APP will be measured throughout ICU stay to test the trial rationale.

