### Methods for additional analyses (e.g., subgroup analyses) {20b}

Subgroup analyses are planned to compare the outcomes of groups of patients with or without serum maximum creatinine ≥ 1.5 mg/dL, maximum or mean IAP value ≥ 16 mmHg before randomization, and baseline or mean APP value < 60 mmHg up to D7.

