## Discussion

This is the first trial to compare the impact of different therapeutic paracentesis strategies on organ dysfunction and outcomes in the prevention and treatment of IAH in critically ill patients with cirrhosis and ascites. Ultimately, we expect to discuss these strategies and improve clinical practice.

Our center has experience in treating critically ill patients with cirrhosis and ascites and IAH and we use both LVP and CPP strategies empirically. The CPP has the potential to minimize IAP, optimize APP, and reduce the number of required abdominal punctures and the risk of perforation and bleeding. However, it may entail higher risk of infection and abdominal wall fistula, when compared to intermittent LVP. The need to better understand the impact of these interventions set the grounds for this trial.

The use of a double lumen catheter for continuous ascitic fluid drainage presents important advantages over a single lumen catheter because: (1) it is more resistant to obstruction by “kinking” due to its internal section pillar and (2) the proximal (lateral) opening is less prone to obstruction by viscera or clotting than the distal (pointing) one. Furthermore, the use of the Seldinger technique to insert the abdominal paracentesis catheter, using an acute angle of percutaneous insertion (ideally, less than 45°), avoiding a perpendicular approach, (1) reduces catheter kinking and (2) may prevent insertion site fistula, given the oblique multiplane closure trajectory. These details are even more important given the duration of the CPP strategy.

The use of IAPC in patients with cirrhosis and ascites has been demonstrated to be safe and effective outside of the ICU setting [20–22]. We do not use prophylactic antibiotics associated with paracentesis in this trial nor in our usual clinical practice. Similarly, in the prevention of catheter-related bloodstream infections, the use of prophylactic antibiotics is not recommended in the clinical management of non-tunneled central venous catheters [28]. Additionally, the use of prophylactic antibiotics in the intervention arm would create a important therapeutic differences between study groups and hinder the comparison of results.

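### The APP subgroup may be defined by mean perfusion pressure up to D7, a post-randomisation value that CPP is expected to change; only the baseline definition is sound

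*Protocol article*

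**What the plan says.** Methods for additional analyses {20b} lists three subgroup variables in one sentence: maximum creatinine at or above 1.5 mg/dL, IAP and APP. The IAP item is "maximum or mean IAP value ≥ 16 mmHg before randomization". The APP item is "baseline or mean APP value < 60 mmHg up to D7". Its opening words, "baseline or mean APP value", admit two definitions.

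Four other places bear on what the APP item means:

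- Outcomes {12} counts D7 from randomisation, which is D0.
- The description of the intervention group states: "The trial intervention catheter will be in place for a maximum duration of 7 days".
- Plans for assessment and collection of outcomes {18a} states: "Intermediate effect variables IAP and APP will be measured throughout ICU stay to test the trial rationale".
- The Discussion states: "The CPP has the potential to minimize IAP, optimize APP".

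**The concern.** A subgroup variable should be fixed before treatment can act on it. Mean APP up to D7 is not: its averaging window coincides with the period in which the CPP catheter may be in place, and changing APP is part of the trial's rationale.

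If CPP raises APP, some CPP patients end up above 60 mmHg who would have stayed below it under large-volume paracentesis (LVP). Suppose also that low APP goes with a worse renal prognosis. The CPP patients left below 60 are then a less favourable selection than the LVP patients below 60. The CPP patients above 60 now include some with a worse prognosis than their LVP counterparts. CPP can then look worse in both strata while the overall difference is zero.

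The window also overlaps the outcome window, since Outcomes {12} uses D1 to D7 summaries and the D7 value. A patient's deterioration can therefore help decide which subgroup the patient is in.

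At stake is a prespecified analysis that readers may take as showing which patients benefit. The wording also leaves open two definitions, one sound and one not, with nothing to say which governs.

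**Working it through.** **Planning figures.** The protocol states no figure for the subgroup analyses. The creatinine scale comes from Sample size {14}: SDs 0.45 and 0.48 mg/dL and a target difference of 0.4. The pooled SD is √[(0.45² + 0.48²)/2] = 0.465. With a noncentral t, one-sided α 0.05 and 95% power, this reproduces the stated total of 60 (power 0.950), so 0.465 is the SD behind the plan.

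**Assumptions not in the protocol.** APP is normal with SD 10 mmHg and control mean 62. CPP raises mean APP by 3 mmHg. APP and outcome correlate at -0.5 (lower APP, higher creatinine). CPP has no true effect on creatinine. The 3 mmHg borrows from "an expected clinically significant IAP decrease of 3 mmHg in the intervention group"; that is an IAP figure, and using it for APP assumes no net change in arterial pressure.

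**Step 1, cut-points in SD units.**
- LVP: (60 - 62)/10 = -0.2, so 42% fall below 60.
- CPP: (60 - 65)/10 = -0.5, so 31% fall below 60.

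**Step 2, mean APP deviation within strata** (φ and Φ are the standard normal density and distribution function).
- Below the cut c, the mean is -φ(c)/Φ(c): LVP -0.929, CPP -1.141.
- Above it, the mean is φ(c)/[1 - Φ(c)]: LVP 0.675, CPP 0.509.

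**Step 3, spurious CPP minus LVP difference in outcome SDs.**
- Below 60: (1.141 - 0.929) × 0.5 = 0.106.
- At or above 60: (0.675 - 0.509) × 0.5 = 0.083.
- With a 5 mmHg rise the same steps give 0.181 and 0.132.

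**Step 4, in mg/dL at the planning SD.**
- 3 mmHg rise: 0.106 × 0.465 = 0.049 and 0.083 × 0.465 = 0.039.
- 5 mmHg rise: 0.181 × 0.465 = 0.084 and 0.132 × 0.465 = 0.061.

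**Step 5, if imputed values widen the SD.** Outcomes {12} assigns 4 mg/dL when RRT or death occurs. Let a fraction p receive that value, and let the rest have mean 1.1 (midpoint of 0.9 and 1.3) and SD 0.465. Then SD = √[(1 - p) × 0.465² + p(1 - p) × (4 - 1.1)²].
- p = 20%: √(0.173 + 1.346) = 1.23, giving 0.106 × 1.23 = 0.13 and 0.083 × 1.23 = 0.10.
- p = 30%: √(0.151 + 1.766) = 1.38, giving 0.106 × 1.38 = 0.15 and 0.083 × 1.38 = 0.11.

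The protocol gives no value for p.

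**Cross-check by simulation** (4,000,000 patients per scenario, no creatinine effect, creatinine SD 0.48). A shared prognostic factor loads 0.3 to 0.7 on both APP and creatinine, which implies an APP-creatinine correlation of magnitude 0.09 to 0.49.

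| APP rise under CPP | Mean APP < 60 | Mean APP ≥ 60 | Baseline APP, either stratum |
|---|---|---|---|
| 0 mmHg | about 0 | about 0 | about 0 |
| 3 mmHg | +0.010 to +0.050 | +0.006 to +0.039 | about 0 |
| 5 mmHg | +0.015 to +0.085 | +0.011 to +0.061 | about 0 |

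Entries are CPP minus LVP in mg/dL; about 0 means within ±0.001. The upper ends agree with Step 4. The overall difference was also within ±0.001 throughout.

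**The case against.** **The sentence may not compare arms.** It speaks of comparing outcomes between patients with and without low APP and does not mention treatment. Read literally, it could be a prognostic comparison, which would fit the general objective of assessing the impact of IAH. The bias described here would then not arise. That reading is possible but less natural: the section is about subgroup analyses, and the same sentence lists both stratification variables. The comparison of arms is therefore an inference, though a reasonable one, and relabelling the mean-APP analysis serves either reading.

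**Baseline APP is already offered.** This stands. Only the mean-to-D7 alternative, and leaving the choice open, is at fault.

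**The size rests on assumptions.** This also stands. A reader might infer a bias of up to a third of the 0.4 mg/dL target. The protocol's own SDs do not support that: they give about 0.04 to 0.05 mg/dL, or 10 to 12% of the target, for a 3 mmHg rise. The larger figure needs an assumed rate of RRT or death. That CPP patients below 60 are sicker likewise depends on the assumed direction of the correlation.

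**The effect is small against noise.** With 35 per arm, 31% and 42% give about 11 and 15 patients below 60. The standard error is √(1/11 + 1/15) = 0.40 SD, so a bias of 0.11 SD is about a quarter of it. This limits the practical weight but does not make the definition sound.

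**The contrast with the other subgroups.** It is clear for IAP. Whether the pre-randomisation limit also covers creatinine is not certain from the grammar, so the point does not rely on it.

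**Conclusion.** The point holds for the mean-to-D7 definition alone. That definition conditions on a variable which the protocol names as an intermediate effect and expects CPP to change, so arm comparisons within its strata lose the protection of randomisation. The bias needs two things: that CPP shifts APP, and that APP shares causes with the outcome. Both belong to the trial's rationale, but neither is quantified in the protocol.

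The illustrative size is 0.11 SD and 0.08 SD for a 3 mmHg rise, with the mg/dL value depending on the endpoint SD as shown in Steps 4 and 5. A reader might infer that the primary result is in doubt. It is not: the randomised comparison of creatinine, the intention-to-treat analysis and the sample size do not use this subgroup. This is a defect in one additional analysis, worth correcting because the rule is stated and the correction is easy.

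**What to change.** In Methods for additional analyses {20b}, define the APP subgroup by baseline (pre-randomisation) APP below 60 mmHg only, as is already done for IAP. Remove mean APP up to D7 from the subgroup list. Report it by arm as an intermediate outcome, or use it in an analysis labelled exploratory or mediational, not as a treatment-effect subgroup. If a prognostic comparison by APP status was intended, say so in those words. The form of the interaction test can be left to the SAP.

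The cost is a change to one phrase. No further data or patients are needed, and the mean-APP information is kept under a label that matches what it can show.

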### Methods in analysis to handle protocol non-adherence and any statistical methods to handle missing data {20c}

Data will be analyzed according to intention-to-treat (ITT). Protocol adherence, with intervention initiation and completeness, will be reported. Missing data will not be imputated and will be described.

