**Methods:**

An investigator-initiated, open label, randomized controlled trial, set in a general ICU specialized in liver disease, was initiated in August 2022, with an expected duration of 36 months. Seventy patients with cirrhosis and ascites will be randomly assigned, in a 1:1 ratio, to receive one of two methods of therapeutic paracentesis. A stratified randomization method, with maximum creatinine and IAP values as strata, will homogenize patient baseline characteristics before trial group allocation, within 24 h of admission.

In the control group, LVP will be performed intermittently according to clinical practice, with a maximum duration of 8 h, while, in the intervention group, continuous passive paracentesis will drain ascitic fluid for up to 7 days.

The primary endpoint is serum creatinine concentration, and secondary endpoints include IAP, measured creatinine clearance, daily urine output, stage 3 acute kidney injury and multiorgan dysfunction assessed at day 7 after enrollment, as well as 28-day mortality rate and renal replacement therapy-free days, and length-of-stay. Prespecified values will be used in case of renal replacement therapy or, beforehand ICU discharge, liver transplant and death. Safety analysis will include paracentesis-related complication rate and harm. Data will be analyzed with an intention-to-treat approach.

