### Criteria for discontinuing or modifying allocated interventions {11b}

The attending physician’s judgment is definitive regarding all clinical decisions, including protocol modification, interruption, or discontinuation, and these should be clearly stated in the patient’s clinical record.

In case of signs of catheter-related complication, particularly in the intervention group, appropriate therapeutic measures should be taken and the paracentesis catheter should be replaced when feasible at a different site for continued protocol intervention.

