## Statistical methods

### Statistical methods for primary and secondary outcomes {20a}

For the descriptive analysis, quantitative variables will be reported as means and standard deviations or as medians and interquartile ranges (*P*_25_-*P*_75_), as appropriate, and categorical variables reported as frequencies and percentages.

Quantitative variables will be analyzed using the assessment day value (D7), the daily mean value, and their maximum or minimum values. Mann–Whitney *U* test will be used to compare study groups, assuming a non-normal distribution, or two independent sample *t*-test, in case of normal distribution. Dichotomous categorical variables will be analyzed using chi-square or Fisher’s exact tests. Using daily values, mixed effects regression models will be used to consider the autocorrelation structure between the longitudinal measurements. Regarding stage 3 AKI as secondary outcome, odds ratios and corresponding 95% confidence intervals will be estimated using logistic regression models. For the study of RRT-free days, competing risks survival models will be applied considering death as the competing risk. Regarding time until death, joint survival regression models will be used to take into consideration the association of longitudinal markers with time until death. For LOS, linear regression models will be applied. For all regression studies, univariable and multivariable analyses will be performed to account for potential confounders. The absolute risk of paracentesis-related complications will be reported for both trial groups. A level of significance *α*= 0.05 will be considered. Data will be analyzed using the R Statistical Software [41].

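### Paracentesis complications are summarised only by allocated arm, so when patients change method a complication can be counted under a procedure that did not cause it; a supplementary table by procedure received is a cheap improvement

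*Protocol article*

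**What the plan says.** All references are to the protocol article.

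- **Analysis principle.** The section on non-adherence and missing data {20c} says "Data will be analyzed according to intention-to-treat (ITT", with no exception for safety. It adds that adherence (initiation and completeness) will be reported. The Methods part of the Abstract puts safety and the principle side by side: "Safety analysis will include paracentesis-related complication rate and harm. Data will be analyzed with an intention-to-treat approach".
- **Harm summary.** Statistical methods {20a}: "The absolute risk of paracentesis-related complications will be reported for both trial groups". No tabulation by procedure received is mentioned.
- **Scope for changing method.** The Discussion says of the centre that "we use both LVP and CPP strategies empirically". Section {11b} says "The attending physician’s judgment is definitive regarding all clinical decisions, including protocol modification, interruption, or discontinuation". Section {11d} places no limits on other care. For the intervention arm, "After the 7th day of intervention, paracentesis should be performed using the standard LVP approach as needed".
- **Expected departures.** Sample size {14}: "We arbitrarily estimate that protocol non-adherence/attrition or violation after randomization may affect approximately 15% of cases".
- **What is expected of harm.** The Discussion anticipates possibly more infection and abdominal wall fistula with CPP, but fewer punctures and less perforation and bleeding. It also admits low power for complications.

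**The concern.** The complications listed under safety procedures in section {11d} are tied to a catheter or a puncture: wall infection, secondary peritonitis, perforation, bleeding and fistula. A count by allocated arm answers a question about strategies. It does not show which procedure produced the event. If a control patient were given a continuous catheter that became infected, the event would be counted under LVP. If a CPP patient had a puncture injury during a later LVP, it would be counted under CPP.

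The Discussion expects the two methods to carry different kinds of risk and gives the need to understand this trade-off as the reason for the trial. Misattributed events blur that trade-off. Harm is also a ground for terminating the trial at the interim analysis after 30 patients, although section {21b} does not say which contrast would be used there.

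**Working it through.** **1. The plan's own figures.** Inputs from Sample size {14}: difference 0.4 mg/dL, SDs 0.45 and 0.48, one-sided alpha 0.05, power 95%, 1:1 allocation.

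- Pooled SD = √((0.45² + 0.48²)/2) = 0.465. The noncentral t calculation gives a total of 60, as stated.
- Allowance of 15%: 60/0.85 = 70.6, or 60 × 1.15 = 69. The stated 70 lies between them, so there are 35 per arm.

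The sample size reproduces. What matters here is that the 15% is a single pooled figure and not a cross-over rate.

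**2. Effect of cross-over on the by-arm comparison.** Let p_C and p_L be the complication risks under CPP and LVP, c_C the share of the CPP arm treated by LVP, and c_L the share of the LVP arm treated by CPP. Assume that risk follows the method received.

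- CPP arm: (1 - c_C)·p_C + c_C·p_L
- LVP arm: (1 - c_L)·p_L + c_L·p_C
- Difference: (p_C - p_L)·(1 - c_C - c_L)

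**3. Size.** The documents give neither complication risks nor cross-over rates. The risks below (20% on CPP, 5% on LVP) are assumptions. The share retained does not depend on them.

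| Cross-over | CPP arm | LVP arm | Difference (points) | Share retained |
|---|---|---|---|---|
| None | 20.0% | 5.0% | 15.0 | 100% |
| 5% in each arm | 19.25% | 5.75% | 13.5 | 90% |
| 15% in CPP arm only | 17.75% | 5.0% | 12.75 | 85% |
| 15% in LVP arm only | 20.0% | 7.25% | 12.75 | 85% |
| 15% in each arm | 17.75% | 7.25% | 10.5 | 70% |

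With other assumed risks, full 15% cross-over in both arms takes 10% v 5% from 5.0 to 3.5 points, and 30% v 10% from 20 to 14 points.

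The last row of the table is the ceiling if the 15% is taken at face value: 0.15 × 70 = 10.5 patients, and c_C + c_L = 10.5/35 = 0.30 however they are split between the arms. If the 15% is all attrition, or violation without a change of method, the loss is 0%.

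**4. LVP after day 7.** This works the other way. A puncture complication after the CPP catheter has been removed, if counted, adds an event to the CPP arm and makes CPP look worse. The article does not say whether complications after day 7 are counted, so the net direction of the error cannot be fixed from the text.

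**5. Precision.** The exact 95% upper limit for zero events is 1 - 0.025^(1/n).

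- n = 35: 10.0%
- n = 15 (about one arm at the interim analysis of 30): 21.8%

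Power at 35 per arm, two-sided 0.05, for 20% v 5% is 47% (normal approximation) or 33% (Fisher) with no cross-over. It is 26% or 15% in the worst row of the table.

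**The case against.** The strongest reply is that this is an omission in a condensed article. A safety set, intervals and a difference are commonly left to the full protocol or analysis plan, which are not shown. Section {20a} says only that risks will be reported, and the Abstract's account of the safety analysis is not exhaustive. This stands for the interval and the risk difference, which are the weaker part of the point. It stands less well for attribution, because the article does state a rule: intention-to-treat without a safety exception, in the section on non-adherence, with harm given per trial group.

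Other replies that stand:

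- A reader might infer that about 15% of patients will switch, so that 15-30% of any excess harm disappears. The text does not support this. The figure is called arbitrary and mixes three kinds of departure, so the range must include zero.
- A reader might infer that the plan necessarily makes CPP look safer. Events after day 7 could do the opposite, and control patients also receive LVP as needed throughout the ICU stay.
- The formula treats each switcher as carrying only the other method's risk. A CPP patient who stops early has already been exposed, and a complication that prompts catheter removal is correctly counted under CPP. Sections {11b} and {11d} provide for replacing a complicated or infected catheter where feasible, which is not a switch to LVP.
- Use of both methods at the centre does not show that control patients will receive CPP catheters. It is possible under the text but not documented.
- A reader might infer that a diluted contrast will drive the harm stop. Section {21b} does not define the contrast, and an independent committee that includes a statistician reviews harm.
- Harm by randomised arm is a legitimate comparison, protected by randomisation.

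**Conclusion.** The point holds in a limited form. As written, complications are summarised by allocated arm with no tabulation by procedure received, in a setting where patients may receive the other method. The loss in a true harm difference from cross-over is between 0% and 30%. This assumes that risk follows the method received and that the pooled 15% bounds the number who cross over; as that figure is itself arbitrary, the ceiling is only as good as the estimate. The net direction is uncertain because LVP events after day 7 would push the other way. The small sample, which the Discussion admits, limits the harm comparison more than dilution does; dilution adds to it. This is a cheap improvement to the safety reporting and not a flaw that invalidates the trial.

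**What to change.** Keep the intention-to-treat table of complications by arm. In sections {20a} and {20c} add:

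- One supplementary table by the procedure in place when the complication arose: CPP catheter, per patient and per catheter-day; LVP, per patient and per puncture. LVP done in a CPP patient after catheter removal is counted under LVP.
- The between-arm risk difference with an exact or score 95% interval, so that a low or zero count is not read as reassurance (0/35 still allows 10.0%).
- A statement that both tables go to the data monitoring committee.

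The cost is a few sentences and one table. Complications are already to be screened actively, and initiation and completeness of the intervention are already to be reported; catheter-days and puncture counts would need to be available from the records. The downside is that the by-procedure comparison is not protected by randomisation, since patients who change method may differ in prognosis. It therefore stands beside the intention-to-treat table and does not replace it.

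### Death before D7 has no rule for the D7 values of IAP, urine output and CLIF-SOFA, and the no-imputation rule then leaves those patients out of three secondary comparisons described as intention-to-treat

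*Protocol article*

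**What the plan says.** The Outcomes section fixes the time point: "The outcomes variables will be assessed at day seven (D7) after randomization (D0), unless otherwise stated". It then deals with events that interrupt follow-up in two rules.

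- ICU discharge or transplant: "Whenever ICU discharge or liver transplant occurs before D7, the last available data prior to these events will be used for outcome assessment". Death is not named here.
- RRT or death: "stage 3 AKI will be considered when RRT or death occurs and, in these circumstances, a serum creatinine concentration value of 4 mg/dL" and a "creatinine clearance value of 10 mL/min will be used for outcome assessment". Only these three renal outcomes receive a value.

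The section on non-adherence and missing data announces an intention-to-treat analysis and adds: "Missing data will not be imputated and will be described". The abstract (Methods) reads more broadly: "Prespecified values will be used in case of renal replacement therapy or, beforehand ICU discharge, liver transplant and death".

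Besides the D7 value, IAP, creatinine, clearance, urine output and CLIF-SOFA "will be analyzed using their maximum or minimum and daily mean values between D1 and D7". The statistical methods section compares groups by Mann–Whitney or t-test and adds mixed-effects models on the daily values.

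**The concern.** A patient who dies before D7 has no IAP, urine output or CLIF-SOFA on D7. No rule supplies a value and imputation is ruled out, so that patient cannot enter the D7 test. The test then compares patients selected by surviving to D7, or by leaving the ICU or being transplanted first. That selection happens after randomisation and can differ between arms.

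The risk is real in this trial. The patients are critically ill, and the hypothesis is that continuous drainage improves organ dysfunction and clinical outcomes, with 28-day survival among the outcomes. The sample size section cites a source in which non-survivors had IAP 3 mmHg higher than survivors, so leaving out deaths is unlikely to be neutral. If one arm keeps more of its sickest patients alive, their poor values count against it. IAP is also the intermediate variable meant to test the trial's rationale.

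**Working it through.** **1. Rules side by side, for the D7 value**

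| Outcome | ICU discharge or transplant before D7 | Death before D7 |
|---|---|---|
| Serum creatinine (primary) | last value | 4 mg/dL |
| Creatinine clearance | last value | 10 mL/min |
| Stage 3 AKI | last value | counted as stage 3 |
| IAP | last value | no rule; not imputed |
| Daily urine output | last value | no rule; not imputed |
| CLIF-SOFA | last value | no rule; not imputed |

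The gap is the last three cells of the right-hand column. The patients in these D7 tests are therefore those not dead before D7, including discharged and transplanted patients with carried-forward values.

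**2. The plan's own figure, and whether power is the issue**

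The plan gives 44 patients for an IAP difference of 3 mmHg, SD 3.9, 80% power, one-sided α 0.05. With 22 per arm the noncentrality is 3 / (3.9 × √(2/22)) = 2.55 on 42 degrees of freedom, and power is 80.6%. The figure reproduces.

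D7 mortality is not in the documents. Assume 10%, 20%, 30% or 40%. Of 70 patients, 63, 56, 49 or 42 remain. One-sided power for 3 mmHg, from Φ(3 / (3.9 × √(2/n)) − 1.645) with n per arm, is 92%, 89%, 85% or 80%. Lost power is not the main problem. Selection is.

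**3. Size of the selection effect on IAP (illustration)**

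Let p be mortality by D7, g the gap in mean IAP between those who die and those who survive, m the mean in all patients and S the mean in survivors. Then m = (1 − p)S + p(S + g), so S = m − p·g. The survivor-only difference (intervention minus control) is off by p_C·g_C − p_I·g_I, roughly (p_C − p_I)·g.

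Assumptions: IAP normal with SD 3.9, and the log-odds of death rising by 3/3.9² = 0.197 per mmHg. This gives g of about 2.7 mmHg, close to the 3 mmHg in the sample size section.

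| Mortality, control v intervention | True difference | Survivor-only difference |
|---|---|---|
| 20% v 20% | 0 | about 0 |
| 30% v 15% | 0 | +0.4 mmHg |
| 40% v 20% | 0 | +0.5 mmHg |
| 20% v 20% | −3.0 | about −3.0 |
| 30% v 15% | −3.0 | about −2.6 |
| 40% v 20% | −3.0 | about −2.5 |

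By the formula, (0.30 − 0.15) × 2.7 = 0.41 and (0.40 − 0.20) × 2.7 = 0.54, in line with the simulation.

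**4. CLIF-SOFA (illustration)**

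Assumptions: underlying D7 score with mean 12 and SD 4, log-odds of death rising by 0.25 per point, mortality 28.6% v 18.0%.

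- Equal underlying scores: survivor means are 11.0 v 11.4, so the arm with fewer deaths looks 0.3 points worse. With deaths set to an assumed maximum of 24, the means are 14.7 v 13.6, which is 1.1 points better.
- Underlying benefit of 0.5 points: survivor-only difference −0.16.
- Underlying benefit of 1 point: survivor-only difference −0.66.

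The shift is about 0.3 points throughout (−0.16 + 0.5 = 0.34; −0.66 + 1 = 0.34). About 35 × 0.714 = 25 and 35 × 0.82 = 28.7 survivors per arm, with SDs near 3.7 and 3.8, give a standard error of √(3.7²/25 + 3.8²/28.7) ≈ 1.0, so the shift is about a third of it. The documents give no input for urine output.

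**The case against.** The best counter-argument is that this is an unspecified detail. No sentence says that patients who die are dropped. The article treats death, discharge, transplant and RRT as events with their own rules, and the abstract states that death has prespecified values. The missing values for three secondary outcomes could sit in a fuller document that is not shown.

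Part of this stands: the abstract shows the intent. But the article does more than stay silent. It lists the outcomes that receive a death value, lists the events that trigger the last-value rule, and then rules out imputation for what remains. A later plan that gave death values for IAP, urine output and CLIF-SOFA would contradict that sentence as it is worded.

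Three stronger readings are tempting and are not supported.

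- A reader might infer that these outcomes lose every patient who died. They do not. The D1–D7 maximum or minimum, the daily means and the mixed models use values recorded before death, and deaths after D7 do not affect the D7 value.
- A reader might infer that the main result is at risk. Creatinine has an explicit death rule.
- A reader might infer that the direction of effect reverses. In the illustration this needs fewer deaths with no underlying effect on the score, whereas the hypothesis expects both to improve. A 0.5-point underlying benefit already restores the right direction. The contrast with deaths scored at 24 also compares two different questions, not a wrong answer with a right one.

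**Conclusion.** The point holds for the single D7 value of three secondary outcomes. As written, those comparisons leave out patients who died before D7, which conflicts with the intention-to-treat statement and with the abstract.

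The size cannot be computed from the documents because D7 mortality by arm is not given. Bias is about zero when mortality is equal. When it differs by 15 to 20 percentage points, it is about 0.4–0.5 mmHg of IAP against the arm with fewer deaths. For CLIF-SOFA it is about 0.3 points at 29% v 18% with equal underlying scores. These figures rest on the assumed mortality, on the assumed link between severity and death, and on carrying over the survivor gap in IAP from the cited source. The bias is small against the sampling error of a 70-patient trial, but it is systematic and cheap to remove. A change is worth making; the primary analysis does not depend on it.

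**What to change.** In the Outcomes section, extend the existing death rule:

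- **CLIF-SOFA and urine output:** death before D7 takes the worst rank, with all such deaths tied, and the arms are compared by Mann–Whitney in all randomised patients.
- **IAP:** the last value before death is used, as is already done for discharge, and labelled as a while-alive value.
- **Survivor-only D7 values** are reported as descriptive.

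In the missing-data section, limit the no-imputation sentence to data missing for reasons other than death, ICU discharge, transplant or RRT. The abstract, the outcome rules and the missing-data rule then agree.

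The cost is two or three sentences. No new data are needed, and the Mann–Whitney test is already in the plan. The downside is that D7 CLIF-SOFA and urine output become composites with death, so a difference may reflect mortality rather than organ function. The descriptive survivor values and the separate 28-day survival outcome help readers tell the two apart.
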